### 2.6. Study Variables

The variables that will be collected are listed in Table 1.

Comorbidity will be assessed using the Cumulative Illness Rating Scale (CIRS), a validated tool used for hospitalized geriatric patients [14]. The disease severity score, ranging from 0 to 4, is based on 14 components reflecting organs impacted by a chronic disease. The CIRS Severity Index measures the number of items with disease severity ratings of three or four. This index is measured on hospital discharge forms at a national level.

To assess the complexity of patients, the score of the Corridor Triage (Tri-Co) instrument will be collected. Tri-Co is composed of the Modified Early Warning Score (MEWS) [15] and the Index of Care Dependency (IDA) [16]. The first tool collects data on clinical stability/instability, while the second one classifies information on care complexity. The integration of those two instruments is justified by the concept that clinical instability and care complexity should naturally complement each other to correctly classify patients according to their level of care intensity and ensure that the provision of care is proportional to the patient’s clinical complexity [17]. Tri-Co has been previously evaluated in several Italian settings [18,19,20]. If Tri-Co is not used in the hospital or wards included in this study, considering the expected heterogeneity in care complexity assessment among hospitals, other validated tools for measuring complexity will be considered. For example, the National Early Warning Score (NEWS), the Index of Care Intensity (IIA), or the Index of Care Complexity (ICA) may be considered [20]. All these measures will be collected as single measures at the beginning and at the end of the patient’s stay and specifically at the time of patient’s admission and the last measurement before discharge, as these assessments are made by nurses to ensure adequate nursing planning.

### 2.7. Procedures

This study started in January 2024 and is planned to end in March 2025. First, a pilot study was conducted to assess the characteristics of the EHR in the enrolled hospitals. Given the lack of a unique national electronic system for storing health information, heterogeneity in the collection and organization of the nursing activities is expected. Therefore, a preliminary meeting was organized with the nursing directors of each hospital. During this meeting, nursing directors described the EHR used in their hospitals. From this information, an electronic dataset was prepared to allow each hospital to enter information on nursing care activities. For each hospital, two medical and two surgical wards will be considered for enrolment. If there are more than two medical/surgical wards in the same department, the two wards with the highest number of patients admitted during the study period will be selected.

Eligible patients will be enrolled by searching the EHR. Data will be collected retrospectively to gather information on nursing care provided in 2022. This study will collect data from all patients included in medical or surgical DRGs. All nursing activities performed on these patients and documented in the EHR will be considered.

Within each hospital, a procedural manager will be designated to extract and de-identify data of interest. The data of patients who meet the inclusion criteria will be transmitted to the principal investigator (PI) by uploading the data into a secure server specific for this study. The upload will take place via a dedicated cloud platform established on an ad hoc basis for the project, allowing each local investigator of the participating centers to access and provide data.

For login purposes, each local investigator will have a username and password (which can be modified by the user after the initial login). Each local investigator will only have access to his or her own uploaded data, while the principal investigator will have access to all the data submitted by each participating center. The Italian Regulatory Board for Nursing Professions (FNOPI) owns the server where the data will be kept. Data gathering will be continuously evaluated, and all disaster recovery measures will be in place. Figure 1 summarizes the steps of the study.

### 2.8. Data Analysis

Descriptive statistics (frequency, percentage, mean, median, range, and standard deviation) will be used to describe the sample. *t*-tests, ANOVA (or related nonparametric tests in case of a non-normal distribution of dependent variables), linear regression, and quantile regression will be performed to evaluate the possible variability in nursing time across hospitals and DRGs.

The chi-square test will be used to analyze any differences in the average frequency of nursing activities within the same DRG. In addition, we will perform linear, logistic and quantile regression, considering cost as the outcome of nursing care. Nursing costs will be assessed across hospitals and DRGs. The quantile regression will be used to explore which factors are associated with the different quantiles of nursing costs.

Nursing costs will be calculated based on several factors, including the average time required to perform each procedure, nurses’ hourly wage, the cost of materials used, and the average length of patient stay. Nursing time will be estimated using a convenience sample of nurses from the hospitals included in this study. For each nursing activity, the participating nurses will indicate the average time spent on the activity and devices relevant to each intervention. Nursing costs will be calculated by applying nurses’ salaries, based on national cost tables for nursing professionals. The annual nursing salary will be used to estimate the cost per minute of nursing time. This cost per minute will then be multiplied by the amount of time spent on each nursing activity and by the total number of activities performed for each patient. Additionally, the cost of devices required to perform each activity will be included, based on prices from the national price list. Thus, the cost per patient per day of hospitalization will be calculated. This cost will enable us to compare patients with different lengths of stay. Finally, subgroups based on patient complexity will be considered.

Moreover, nursing costs will also be compared between patients with chronic and acute diseases. This will allow us to explore the hidden nursing costs derived from the nursing care delivered on an ongoing basis for chronic diseases (e.g., symptom monitoring, administration of medication for the chronic disease, etc.) that did not show signs of exacerbation during hospitalization. A subgroup analysis will be considered to determine which patients require more nursing care (in terms of time and costs). The nursing case mix (i.e., the patient characteristics that best explain the amount and costs of nursing care) will be evaluated to provide evidence for separating out nursing care activities and nursing intensity in the Italian prospective payment system.

To enable accurate data analysis, the need to normalize scores obtained from different rating scales measuring the same outcome will be evaluated. If information from the retrieved nursing records is missing, a missing value analysis will be performed to assess the appropriateness of multiple imputation [21]. Specifically, the reason for missingness will be examined, followed by the analysis of fraction of missing information and assessment of auxiliary variables to be used for multiple imputation. Then, sensitivity analyses involving several imputation models may be performed based on missing value analysis. Patients with missing data from all variables retrieved from the nursing record (i.e., missing data on nursing activities, nursing assessment and patient complexity) will be excluded. All descriptive and inferential analyses will be performed using R V. 4.4.2 [22] or similar software. The level of significance for all analyses will be fixed at *p* < 0.05.

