## 1. Introduction

The current healthcare system is facing a complex challenge, with rising costs and the need for improved quality of care [1]. This is exacerbated by the growing complexity of patient conditions, particularly chronic illnesses and an aging population, which put pressure on healthcare systems [2].

To maintain the sustainability of public finances, it is crucial to monitor public health expenditure. Governments reimburse health service expenditure through specific reimbursement systems, such as the Diagnosis-Related Group (DRG) system. The DRG system was created to maintain sustainable inpatient procedures, control healthcare costs, and categorize inpatients based on clinical and treatment criteria. Patients in the same group are expected to use similar resources, encouraging clinicians to effectively manage costs [3,4]. However, this system does not include the costs of nursing care [5].

Nurses are the largest professional group in the healthcare system. However, very little is known about the cost and quality of nursing care, and more specifically, the effectiveness of the care provided by each nurse [5]. In almost all countries, nursing care costs are considered a service cost and are included in the DRG system, similarly to hospitals’ other fixed costs [3]. The DRG system estimates the cost of hospital nursing care based on the total number of nurses assigned to inpatients. Consequently, nursing care costs are calculated as an average lump sum that does not take into account care intensity, the level of patient dependency, the variability in nursing resource consumption, and the intrinsic and intangible characteristics of nursing care [6]. This implies that the amount of nursing care may vary considerably even within the same DRG [7].

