## 2. Materials and Methods

### 2.1. Aims

The primary aims of this study are (1) to assess the variability of nursing costs between different DRGs and within the same DRG; and (2) to measure how much variability in the intensity of nursing care is explained by DRGs.

The secondary objectives of this study are (1) to measure the amount of nursing activity in acute care hospitals; (2) to examine the variability of the intensity of nursing care activities by DRG within patients and across patients controlling for hospital and region; and (3) to identify and quantify any differences in care needs among patients discharged with the same DRG.

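### Section 2.8 makes non-normality the only stated reason to leave the t-test or ANOVA; unequal spread across DRGs is not addressed, and the rank-test fallback does not cover it

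*Protocol article*

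**What the plan says.** Section 2.8 (Data Analysis) assigns t-tests, ANOVA, linear regression and quantile regression to nursing time across hospitals and DRGs. The condition for leaving the t-test or ANOVA is in a parenthesis: "ANOVA (or related nonparametric tests in case of a non-normal distribution of dependent variables), linear regression, and quantile regression will be performed". No other condition is given. For cost, the same section says "we will perform linear, logistic and quantile regression, considering cost as the outcome of nursing care". Results are judged at p < 0.05 throughout ("The level of significance for all analyses will be fixed at" that level).

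The first primary aim in section 2.1 is "to assess the variability of nursing costs between different DRGs and within the same DRG". The Introduction expects that "the amount of nursing care may vary considerably even within the same DRG".

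The article does not mention variance form (pooled or Welch), standard-error type, or a check for unequal variance.

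**The concern.** The classical t-test, one-way ANOVA and ordinary least squares standard errors use one residual variance for all groups. That assumption is fragile here for two reasons.

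- **Spread.** Section 2.8 builds cost from minutes per activity, number of activities and devices. Sums over counts usually have a larger SD where the mean is larger, so DRGs with more nursing activity would tend to be more variable.
- **Size.** Every eligible patient in two medical and two surgical wards per hospital is taken (section 2.7), with no quota per DRG. Common and rare DRGs will differ greatly in numbers.

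The error from unequal spread combined with unequal size does not shrink as the sample grows, so the expected 15,000 or more patients (section 2.9) do not remove it. Non-normality, the one condition the plan checks, matters less for means of well-filled groups. At stake is which DRGs are declared to differ in mean nursing time, and how precise the regression estimates of time and cost appear.

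**Working it through.** **Inputs.** From the article: the tests named, the single trigger, and the 0.05 level (taken as two-sided). The article gives no SDs, number of DRGs or DRG sizes, and no power figure, so there is no stated figure to reproduce. All SD ratios and group sizes below are assumptions.

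**Step 1: pooled t-test, large-sample formula.** With sizes n1, n2 and SDs s1, s2:

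- pooled variance vp = (n1·s1² + n2·s2²)/(n1 + n2)
- squared standard error used = vp·(1/n1 + 1/n2)
- true squared standard error = s1²/n1 + s2²/n2
- type I error = 2·(1 − Φ(1.96·R)), where R is the standard error used divided by the true one

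Take n1 = 400 with SD 1 and n2 = 100 with SD 2. Then vp = (400 + 400)/500 = 1.6. The squared standard error used is 1.6 × 0.0125 = 0.0200 and the true one is 0.0025 + 0.0400 = 0.0425. R = √(0.0200/0.0425) = 0.686, and the type I error is 0.179. With the larger SD in the larger group, R = √(0.0425/0.0200) = 1.458 and the error is 0.004.

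| SD ratio | Sizes | Smaller group more variable | Larger group more variable |
|---|---|---|---|
| 1.25 | 4:1 | 0.086 | 0.025 |
| 1.5 | 4:1 | 0.121 | 0.013 |
| 2 | 4:1 | 0.179 | 0.004 |
| 2 | 10:1 | 0.252 | 0.001 |
| any | 1:1 | 0.050 | 0.050 |

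**Step 2: one-way ANOVA, skewed data, identical means.** 30 DRGs of 40 to 1,000 stays (9,178 in total), gamma outcomes, coefficient of variation from 0.3 to 0.6, 1,500 runs per setting. Ranges are over repeated simulations.

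| Pairing of spread and size | Classical ANOVA rejects |
|---|---|
| Small DRGs more variable | 41-44% |
| Large DRGs more variable | 0.2-0.5% |
| Unrelated | about 6-8% |

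Welch ANOVA rejects in about 4-6.5% across these settings.

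**Step 3: one-way ANOVA, normal data.** 50 DRGs of 47 to 933 patients (14,999 in total), 20,000 runs.

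| Ratio of largest to smallest SD | Small DRGs more variable | Large DRGs more variable | Equal sizes |
|---|---|---|---|
| 1 | 0.051 | 0.050 | 0.049 |
| 1.25 | 0.143 | 0.014 | 0.050 |
| 1.5 | 0.275 | 0.005 | 0.056 |
| 2 | 0.540 | 0.002 | 0.061 |

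Welch ANOVA stays at 0.048 to 0.054 in all these settings and at a threefold SD range.

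**Step 4: the stated fallback.** For two symmetric groups with the same centre and an SD ratio of 2, Mann-Whitney rejects in 11.5% (sizes 400 and 100, smaller group more variable) or 1.7% (reverse). Welch t gives 5.2% and 5.7%. In the skewed setting of step 2, Kruskal-Wallis rejects in about 48-88% of runs although all means are equal. Those are not false positives for the rank test's own null hypothesis, because the distributions do differ. They show that it answers a different question from equality of means.

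**The case against.** A reader might infer more than the article supports, on three counts.

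- **That primary aim 1 declares spreads to be unequal.** It does not. Section 2.1 and the Introduction speak of variation within a DRG. Large within-DRG variation is compatible with one common variance, so unequal spread is a plausible assumption of this review.
- **That pooled forms are prescribed.** They are not. Welch versions are also t-tests and ANOVA, and linear regression can carry robust standard errors. That choice is commonly left to a full protocol or SAP, neither of which is shown, so silence on it is no error.
- **That error rates will be wrong in both directions.** Any one comparison errs in one direction at most. The large figures need pooled forms, unequal SDs and sizes aligned with those SDs. With equal sizes the pooled t-test is unaffected and ANOVA only mildly so.

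Two further defences carry weight. Quantile regression, planned for both time and cost, needs no common spread. And t-tests and ANOVA are named for time only; for cost the exposure is through the linear regression.

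All of this stands. What it leaves is the one rule the article does state: a switch on non-normality to a rank test. Nursing time is likely to be skewed, so the switch is likely to be used, and it neither handles unequal spread nor keeps the comparison on means. Quantile regression does not correct the mean-based tests.

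**Conclusion.** The point holds as a cheap improvement, not as a statement that the plan is wrong as written. The stated switching rule checks the less damaging assumption and moves to a test that does not compare means. If pooled forms are used and spread is related to DRG size, type I error can be several times 5% or close to zero; if spread is unrelated to size, the excess is small. The sizes rest entirely on assumed SDs and DRG sizes. What does not rest on them is that non-normality is the only stated trigger and that the rank-test replacement leaves unequal spread unhandled.

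**What to change.** In section 2.8:

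1. Specify Welch t-tests and Welch ANOVA for comparisons of mean nursing time.
2. Specify heteroscedasticity-consistent standard errors, or cluster-robust ones, for the linear regressions of time and cost. With five hospitals and four wards each (5 × 4 = 20 wards), clusters are few, so a cluster-robust version needs a small-sample correction.
3. Drop non-normality of the dependent variable as the sole trigger for changing method. Where rank tests are kept, say that they compare distributions and not means.

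This is a wording change and different function options in R; no new data are needed. The price is a slight loss of power if variances turn out equal. Welch methods also need a variance from each DRG, so the text should say how DRGs with very few stays are handled.

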### 2.3. Study Setting

A random sample of 5 public acute hospitals will be selected from the total number of potentially eligible hospitals that have expressed interest in participating in this study. To ensure representativeness across Italy, one hospital will be chosen from each geographical area identified according to the classification of the Italian National Institute of Statistics (ISTAT):Northwest (Liguria, Lombardia, Piemonte, and Valle d’Aosta);Northeast (Emilia-Romagna, Friuli-Venezia Giulia, Trentino-Alto Adige, and Veneto);Central (Lazio, Marche, Tuscany, and Umbria);South (Abruzzo, Basilicata, Calabria, Campania, Molise, and Puglia);Islands (Sicily and Sardegna).

To ensure randomization when selecting the sample of hospitals, a comprehensive list of all public hospitals that expressed interest in participating in this study across the five geographical areas of Italy will be created. Then, we will use stratified random sampling to randomly select one hospital from each area, employing a random number generator to eliminate bias.

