### 2.5. Eligibility Criteria for Patients

All data regarding included patients admitted and discharged in the year 2022 will be collected. Data will be collected from patients who meet the following inclusion criteria: (a) patients with medical or surgical DRGs (selected by the department code on the hospital discharge form) with a length of stay > 1 day; (b) patients whose admission and discharge took place in the same ward; and (c) patients admitted and discharged in 2022. Patients aged < 18 years will be excluded.

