### 2.9. Source of Bias

The potential sources of bias in this study will include selection bias due to the proposed convenience sample, which will consist of five public hospitals in Italy. However, we expect to collect a substantial amount of data from patients across all geographical areas of Italy, with an estimated sample size of at least 15,000 individuals. Data collection bias may also arise from retrospective data collection, where incomplete records could affect the results, leading to inconsistencies in estimating the amount of nursing activities digitally registered and the related nursing costs. This bias will be controlled by performing multiple data imputation. Contextual biases related to institutional policies and healthcare culture may also influence nursing practices and patient care across different hospitals. Therefore, a thorough examination of institutional policies and healthcare cultures will be required to address contextual biases during data analysis. A potential source of bias is that the estimated nursing costs are based on a convenience sample of nurse estimates. This approach may not accurately capture the variability in nursing care across different settings. As a result, there is a risk of either overestimating or underestimating nursing costs, depending on how accurately nurses report the time spent on various activities. Thus, the development of standardized data collection guidelines, and the provision of comprehensive training for staff, will be essential to ensure consistency and accuracy in records, thereby minimizing measurement bias related to the reporting of nursing activity time. Finally, the implementation of ongoing evaluation and feedback mechanisms will further help identify and correct biases throughout the research process.

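### Section 2.8 names patient-level tests and regressions at p < 0.05 although patients are nested in 20 wards of 5 hospitals; no named method accounts for ward, and no statistic is tied to primary aim 2

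*Protocol article*

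**What the plan says.** **Design.** Section 2.3 selects five hospitals: "one hospital will be chosen from each geographical area identified according to the classification of the Italian National Institute of Statistics". Section 2.7 adds: "For each hospital, two medical and two surgical wards will be considered for enrolment". Section 2.5 admits only "patients whose admission and discharge took place in the same ward", so each patient belongs to exactly one ward. Section 2.9 expects a large yield, "with an estimated sample size of at least 15,000 individuals".

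**Aim.** The second primary aim in section 2.1 is "to measure how much variability in the intensity of nursing care is explained by DRGs".

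**Analysis.** Section 2.8 names t-tests, ANOVA or nonparametric equivalents, and then "linear regression, and quantile regression will be performed to evaluate the possible variability in nursing time across hospitals and DRGs". It adds a chi-square test for activity frequencies within a DRG, and linear, logistic and quantile regression for cost. Its only general criterion is: "The level of significance for all analyses will be fixed at *p* < 0.05". It names no ward term, random effect, clustered standard error, R-squared or variance component.

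**Hospital.** Secondary objective 2 (section 2.1) adjusts for hospital and region. Section 2.9 says that differences in institutional policy and culture are to be examined during the analysis, but does not say how.

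**The concern.** Patients in one ward share staff, routines and a recording system, so their nursing minutes and costs will tend to be alike. In their standard form, the named tests treat patients as independent. When whole wards or hospitals are compared, the information is limited by the number of wards (20), not the number of patients (15,000). The usual p-values and intervals then claim far more precision than the data hold.

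Adjusting for hospital leaves the differences between wards of one hospital untouched. With one hospital per area, hospital and region are also the same five categories, so they cannot be separated as two terms.

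Aim 2 asks for a share of variability. Without a named statistic, the share could be reported in several ways that give different answers. It matters because the results are meant to inform how nursing care enters DRG payment.

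**Working it through.** **1. Inputs from the article.** 5 hospitals (2.3); 2 medical + 2 surgical wards each (2.7); at least 15,000 patients (2.9), stated as an expected yield without inputs, so there is no calculation to reproduce; significance level 0.05 (2.8), taken as two-sided.

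**2. Assumptions.** The article gives neither an ICC nor a number of DRGs. Ward ICCs of 0.001 to 0.10 are used as a range, with wards of equal size.

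**3. Clusters.** 5 × 4 = 20 wards; m = 15,000 / 20 = 750 patients per ward.

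**4. Design effect for a contrast between wards.** DEFF = 1 + (m − 1) × ICC = 1 + 749 × ICC. The true standard error is √DEFF times the naive one, and the effective n is 15,000 / DEFF. The real two-sided error of a nominal 5% test, for example medical against surgical wards, is 2 × [1 − Φ(1.96 / √DEFF)].

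**5. Naive hospital ANOVA with no true hospital effect.** The F statistic on 4 degrees of freedom is inflated by about DEFF, so its false-positive rate is about P(χ²₄ > 9.488 / DEFF). At ICC 0.01 this is P(χ²₄ > 9.488 / 8.49) = P(χ²₄ > 1.118) = 0.89.

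| Ward ICC (assumed) | DEFF | SE factor | Effective n | Real error, ward-level contrast | False positives, hospital ANOVA |
|---|---|---|---|---|---|
| 0.001 | 1.75 | 1.3 | 8,576 | 0.14 | 0.25 |
| 0.01 | 8.49 | 2.9 | 1,767 | 0.50 | 0.89 |
| 0.05 | 38.45 | 6.2 | 390 | 0.75 | 0.99 |
| 0.10 | 75.90 | 8.7 | 198 | 0.82 | 0.998 |

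Simulation of 5 hospitals × 4 wards × 750 patients agrees with the last column. At ICC 0 the rate is about 5%, so the inflation comes wholly from the assumed ward differences.

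**6. DRG comparison with no true DRG effect.** This was simulated with 10 medical and 10 surgical DRGs (an assumption), 200 runs per scenario, and equal ICCs at ward and hospital level. Each range runs from a similar to an uneven DRG mix across wards of the same type.

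| ICC at each level | ANOVA, no adjustment | Hospital fixed effects | Ward fixed effects |
|---|---|---|---|
| 0.01 | 0.34–0.95 | 0.33–0.77 | 0.06–0.07 |
| 0.05 | 0.60–1.00 | 0.60–1.00 | 0.04–0.05 |

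Hospital adjustment alone does not restore the error rate. A ward term does, because DRGs are then compared within wards.

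**7. Share explained by DRG.** With N = 15,000 and an assumed 40 DRGs, p = 0.05 is reached at R² = 0.4%. A significant DRG test therefore says almost nothing about the share. With a true DRG share of 10% and an uneven mix (100 runs), unadjusted R² averaged 11.8% at ICC 0.05 + 0.05 (ward + hospital) and 13.9% at 0.10 + 0.10. With a similar mix across wards it averaged 10.5% and 11.0%.

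**The case against.** The strongest reply is that section 2.8 lists families of methods and never says that patients are independent. Linear or quantile regression with ward terms or clustered errors is still linear or quantile regression, and such detail is often left to an analysis plan, which is not shown here. This has some force for the regressions. It has little for the t-tests, ANOVA and chi-square test, which are named outright and in ordinary form make no allowance for clustering. The article fixes those tests against a ward-based sample that it also fixes.

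Three stronger readings are tempting, and the article does not support them.

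- *All intervals are far too narrow.* The size depends on an ICC that is not given, and DRGs compared within the same wards are little affected.
- *Hospital is ignored.* Secondary objective 2 adjusts for it, and time and cost are compared across hospitals.
- *Aim 2 will be decided by p < 0.05.* The article sets a significance level but never makes it the answer to aim 2, and the named linear regression can yield R-squared.

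It is also fair to say that the total share explained by DRG, ward placement included, is a legitimate target for a payment question. That is a reason to report the unadjusted share beside the adjusted one, not to leave the choice open. Finally, the large hospital-ANOVA figures concern a comparison that is planned but is not a primary aim.

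**Conclusion.** The point holds in limited form. As written, the named tests do not match a sample of 20 wards. For hospital, medical-versus-surgical and ward-concentrated DRG contrasts the standard errors are too small: by a factor of 1.3 at an assumed ward ICC of 0.001, 2.9 at 0.01 and 6.2 at 0.05. Even the smallest of these takes the hospital ANOVA to about five times its nominal error. Hospital adjustment does not cure this. The figures rest on assumed ICCs and equal ward sizes, and the simulations in step 6 and for R-squared also on an assumed number and mix of DRGs.

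For aim 2 the fault is narrower: no statistic is tied to the aim, and the obvious default, unadjusted R-squared, absorbs ward differences when DRG mix varies by ward. In the scenarios tried, that bias was 1.8 to 3.9 percentage points on a true 10% with an uneven mix, and 1 point or less with a similar mix.

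**What to change.** - Replace the naive tests with models that account for ward: hospital as a fixed effect and ward as a random effect, or small-sample-corrected ward-clustered errors, or a ward bootstrap. Apply this to quantile regression too.
- Do not enter hospital and region as two separate terms.
- Present hospital comparisons as descriptive, or test them with ward-level degrees of freedom: 20 − 5 = 15 in the denominator, not about 15,000.
- Name the statistic for aim 2: the DRG share of variance (variance component or adjusted R-squared) with a 95% CI, both unadjusted and after ward and hospital.
- Keep a ward code in the extract. Table 1 does not list one, although ward selection and the same-ward criterion already require it.

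No further patients are needed. The price is wider intervals and fewer significant results.

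### The chi-square test planned for average activity frequency within a DRG does not fit that quantity: it is too liberal if activities are pooled, and tests something else if patients are classified

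*Protocol article*

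**What the plan says.** All the statements are in section 2.8 (Data Analysis) unless noted.

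- Activity frequency: "The chi-square test will be used to analyze any differences in the average frequency of nursing activities within the same DRG". What is cross-tabulated, activities or patients, is not stated.
- Unit of the data: cost is built from time per activity multiplied "by the total number of activities performed for each patient", so each patient carries a count, usually of many activities. Table 1 lists the number of activities by DRG among the nursing-record variables.
- Nursing time: t-tests, then "ANOVA (or related nonparametric tests in case of a non-normal distribution of dependent variables), linear regression, and quantile regression". The outcome named in that sentence is time, compared between hospitals and between DRGs.
- Cost: "we will perform linear, logistic and quantile regression, considering cost as the outcome of nursing care". No binary version of cost is defined. Cost is expressed per patient per day so that stays of different length can be compared. No similar step is given for activity counts.
- Error rate: "The level of significance for all analyses will be fixed at *p* < 0.05".
- Section 2.1 gives, as the third secondary objective, finding and quantifying differences in care needs among patients with the same DRG. The Introduction argues that the amount of nursing care may differ considerably even inside one DRG.

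**The concern.** A chi-square test compares how independent units fall into categories. An average number of activities per patient is not a category count, and the activities of one patient are not independent of each other: a dependent or unstable patient generates more of them throughout the stay. They also accumulate with days in hospital, so a difference in counts may only reflect a difference in length of stay.

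Two implementations are open. Pooling activities into a table makes each activity an independent observation and understates the variance of the totals. Classifying patients into categories respects the unit of observation but changes the question. At stake is the direct comparison of activity frequency within a DRG, which bears on the third secondary objective.

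**Working it through.** **No figure to reproduce.** The protocol gives no effect size, standard deviation or power for this comparison. The only relevant number is the nominal 5% level. The mean count, the between-patient coefficient of variation (CV) and the number of patients per group are assumptions. The five hospitals come from section 2.3.

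**Pooled table, two groups.** Let a patient's rate vary with mean m and coefficient of variation CV, and let the count be Poisson given that rate. The variance-to-mean ratio is

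phi = 1 + m × CV².

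With equal group sizes and no true difference, the pooled statistic behaves as phi times a chi-square variable with 1 degree of freedom. The true size of the nominal 5% test is therefore

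2 × P(Z > 1.96 / √phi).

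| m | CV | phi | 1.96/√phi | True size |
|---|---|---|---|---|
| 5 | 0.3 | 1.45 | 1.628 | 0.104 |
| 5 | 0.5 | 2.25 | 1.307 | 0.191 |
| 50 | 0.3 | 5.5 | 0.836 | 0.403 |
| 50 | 0.5 | 13.5 | 0.533 | 0.594 |
| 100 | 0.3 | 10.0 | 0.620 | 0.535 |
| 100 | 0.5 | 26.0 | 0.384 | 0.701 |

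A gamma-Poisson simulation (20,000 replicates, 50 patients per group) gave 0.398 (m 50, CV 0.3), 0.600 (m 50, CV 0.5) and 0.702 (m 100, CV 0.5), in agreement. The number of patients does not enter the formula, so a large study does not cure the inflation.

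**Pooled table, five hospitals.** With 4 degrees of freedom the size is P(χ²₄ > 9.488 / phi). A simulation of 4,000 runs with 60 patients per hospital is set beside it.

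| m | CV | phi | Formula | Simulated |
|---|---|---|---|---|
| 20 | 0 | 1.0 | 0.050 | 0.046 |
| 5 | 0.5 | 2.25 | 0.377 | 0.388 |
| 20 | 0.3 | 2.8 | 0.495 | 0.495 |
| 20 | 0.5 | 6.0 | 0.812 | 0.804 |
| 100 | 0.5 | 26.0 | 0.985 | 0.984 |

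The first row is the case in which all patients share one rate; there the pooled test is valid.

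**Patients as the unit.** In the same simulations, over means of 5 to 100 and CV from 0 to 1, a chi-square test on patients split at the median count had size 0.048 to 0.056. ANOVA on per-patient counts had 0.046 to 0.054. These are close to nominal, but the median split compares the proportion of patients above a threshold, not an average.

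**Length of stay.** Two patients with the same daily rate, one staying 4 days and one 12, have expected counts in the ratio 1 to 3. Neither chi-square version separates this from a difference in daily care.

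These simulations omit ward and hospital clustering. They isolate the effect of treating activities as independent.

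**The case against.** The strongest reply is that the protocol does not say activities will be pooled and gives no dispersion figure, so inflation is not a stated property of the plan. With patients as the unit, the test keeps its level. Means of 50 to 100 may also be high when each activity type is analysed separately, and at a mean of 5 the two-group inflation is moderate. All of this stands, and it is why the size is given as a range that depends on pooling. It does not rescue the sentence: the version that keeps its level does not test an average, and equal rates across patients would contradict the study's own rationale in the Introduction.

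It may also be said that a condensed article leaves details to an analysis plan. That holds for multiplicity control, the choice of model family for cost and the form of standard errors. It does not hold for the test itself, which the article names.

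Three stronger readings are tempting, and the document does not support them.

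- A reader might infer that rank tests are planned for cost. The nonparametric fallback is in the sentence on nursing time; none is stated for cost.
- A reader might infer that mean cost would go unestimated. Linear regression is planned for cost, and for time, alongside quantile regression, which suits skewed data.
- A reader might infer that the results on within-DRG differences would be mostly false positives. A type I error rate does not give the share of positive results that are false; that also needs the proportion of true nulls and the power, and neither is available. The complexity measures, subgroups and case-mix evaluation also bear on this objective.

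**Conclusion.** The mismatch between test and quantity is a fault in the plan as written, whichever table is used. The error-rate inflation is conditional: it requires pooling of activities and patient rates that differ. Under those conditions and the assumed CVs of 0.3 to 0.5, a two-group test at nominal 5% has a size of about 10% to 19% at a mean of 5 and about 40% to 70% at means of 50 to 100, with larger values for five hospitals. If patients are classified, there is no inflation, but the stated question is not answered. In both cases length of stay is ignored and no effect size is produced, although the objective asks for differences to be quantified.

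The consequence is confined to one secondary analysis; the primary cost analyses are not undermined by this point. As a minor matter, logistic regression on a continuous cost cannot be run until a binary cost is defined. The model can be a reasonable supplement, for instance for high-cost patients, so the need is a definition and not removal.

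**What to change.** In section 2.8, replace the chi-square test with a patient-level count model for each activity: negative binomial or quasi-Poisson, with log length of stay as offset and errors that allow for clustering by ward or hospital. Report rate ratios with confidence intervals for the comparisons within a DRG. Name the groups being compared.

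State in advance how cost is made binary for the logistic model.

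The change is to analysis wording. It needs no new data, because activity counts and admission and discharge dates are already collected (Table 1). The price is slightly more analysis work and fewer nominally significant results. With only five hospitals, errors clustered at hospital level will rest on few clusters, so the level of clustering should be chosen with that in mind.
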